### Sample measurement

G*Power 3.1.9.2 was used to perform the power calculations. The change of Cobb angle was the primary outcome measurement. The results of our previous study showed that the change of Cobb angle in the experimental group was − 1.55 ± 4.39 degrees, whereas in the control group, it was 2.90 ± 2.60 degrees [25]. The α will be 0.05, and the β will be 0.05. Therefore, we should recruit 19 patients to each group. Considering 10% potential attrition, 21 patients per group will be recruited.

### Data collection, data management, and statistical analysis plan

The primary outcome is the change of Cobb angle, and the secondary outcome measures will include the ATR, sagittal index, and quality of life. Descriptive statistics will be calculated for baseline demographics, physical examination, radiographs, and questionnaire data, and results will be presented as the mean ± SD, whereas categorical variables will be expressed as percentages. The chi-squared test will be used to compare the categorical/dichotomous variables. Separate analyses will be conducted for each outcome.

Data will be entered using EpiData software designed for this study. All data will be collected, typed, and analyzed by a masked statistician who will not have access to study assignment. The main investigators will check the data every 2 weeks to ensure the quality.

The primary endpoint is the pre- and posttreatment difference in the Cobb angle. We have calculated that a sample size of 21 patients per group would be capable of detecting a between-group difference of 5 degrees in the primary endpoint with a type I error of 5% and a power of 95% [20]. Because the interval of Cobb angles at entry is 10–20 degrees, and assuming a uniform distribution of Cobb angles in this range (the most unfavorable scenario), an SD of 5 degrees is estimated [8].

Baseline comparability will be assessed using Student’s *t* test for independent samples. To screen for variables associated with each of the outcome variables, univariate linear mixed models for each relevant covariable (age, gender, body mass index, Risser sign, time since menarche, apex levels, curve pattern, and compliance may have associations with risk of progression) will be conducted.

Multiple linear mixed models for each time point will be tested, including covariables found significant at *p* ≤ 0.20 in the univariate analysis, and after screening for multicollinearity [42].

For the ordinal outcome (SRS-22, which is based on only one item with five levels), generalized linear mixed effects model analysis will be used.

Furthermore, because subjects with younger than 13 years of age are characterized by a higher risk of progression [43], the patients will be divided into two subgroups (age < 13 years and age ≥ 13 years), and a linear mixed model analysis for the primary outcome will be performed on each subgroup.

To assess differences in group changes from baseline to 6 months while adjusting for covariables, weighted estimating equations and a sensitivity analysis will be conducted as the primary approach to deal with the missing data, especially for the primary outcome of Cobb angle [44]. All the analysis will be carried out using IBM SPSS Statistics for version 20.0 software (IBM, Armonk, NY, USA).

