### Randomization and masking

After an initial assessment examination confirming eligibility and collection of baseline data, participants will be allocated by a physician using computer-generated block randomization in a ratio of 1:1 to the experimental group or control group. The allocations will be concealed in sequentially numbered, opaque, sealed envelopes with a signature across the sealing point.

Because of the nature of the intervention, physical therapists and patients cannot be blinded when offering or receiving the treatment. However, patients will be asked not to reveal their group allocation to ensure blinding of the evaluator. To minimize bias, strict eligibility will be maintained in the whole trial, and there are separate rooms for assessment and treatment, so that each group will hardly know much about each other. A trained evaluator blinded to group allocation will complete all patient assessments at baseline and immediately after the 6-month intervention. Both groups will continue with their routine activities, but they will not be able to attend any other formal exercise program. The statistician will not be aware of the data coding. Figure 2 illustrates the timing of all trial processes (Additional file 2).

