### Intervention

#### Experimental intervention program

The experimental group will receive a modified physiotherapeutic scoliosis-specific exercise intervention: the three-dimensionally integrated exercise for scoliosis program, which includes autocorrection in three dimensions, postural correction, breathing training, resistance training, muscle fascia releasing, functional activities, balance training, core stability training, proprioceptive input exercises, and patient education. Autocorrection exercise in three dimensions will be combined with specific breathing mode, and isometric contraction training to correct abnormal spinal physiological curvatures in the sagittal plane, accompanied by a wedge pad to modify humpback, waist asymmetry, and pelvic rotation in the horizontal plane. In breathing pattern training, the physical therapist will stimulate the concave areas of the thorax for patients during deep inspiration and will transfer stimulation to the convex side during deep expiration. While the patient is in coronal plane with longitudinal axial stretching, pelvic adjustments will be made to reduce the lateral curvature. During this period, the physical therapist will teach the patient how to combine these exercises with activities of daily living. All the patients in the experimental arm will receive treatment of one or two sessions weekly in the hospital under the supervision of a physiotherapist and one session per day at home under parental supervision. Some examples are shown in Fig. 3.

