### Control group program

Control subjects will receive the standard of care according to the SRS criteria: observation for patients with curves between 10 degrees and 25 degrees [9] and attendance at the study assessments. The control group will only attend study assessments and not the therapy sessions.

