### Compliance supervision

Compliance will be monitored using a home training diary to record the time and frequency of every-day home training, verified daily by a parent and weekly by a therapist. Meanwhile, all the patients will be added to Micro Message Platform app created by the research assistant. The assistant will divide the patients into two groups following their allocation and check the daily training at irregular intervals, answer patients’ questions online, share health knowledge with the patients, or remind the patients to attend clinic visits after the 6-month intervention. To maximize compliance, the physical therapist will provide home equipment, provide the patients with access to facilities, change the exercises to improve compliance with exercises to avoid patients’ getting bored with always performing the same exercises, and encourage parents to be fully engaged to ensure the exercises are regularly performed at home. Attendance will be calculated as a percentage of the prescribed visits attended, and compliance will be calculated as a percentage of the prescribed home exercise dose completed over the course of the 6 months of treatment. When compliance drops below 70%, the physical therapist will try to resolve the issues cooperatively with patients and parents [29, 30].

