### Interim analysis

An interim analysis will be performed on the primary endpoint of Cobb angle when enrolling 20 patients, including control group and experimental group, by a single statistician who is blinded to allocation and reports the results to the main investigators. The main investigators will discuss the results of the interim analysis with the monitoring board. In this study, the change of Cobb angle is the only primary outcome measurement; the secondary outcome measurements are the supporting elements for the whole outcome.

Our primary hypothesis is that the experimental intervention of three-dimensionally integrated exercise for scoliosis will optimize improvement in outcome effects (reduction in Cobb angle and improvement in multifidus activation). Effect sizes will be estimated using Cohen’s *d*, which corresponds to the mean difference between the groups in the change observed from baseline to 6 months (three-dimensionally integrated exercise for scoliosis standard of care), divided by the pooled SD at baseline (Cohen’s *d* ≥ 0.8 = large, 0.5–0.8 = moderate, 0.2–0.5 = small [45]). According to the previous study, the perceived mean global rating of change in the specific exercise group was 3.8 ± 2.2, corresponding to moderate improvement, and 0.3 ± 1.7 in the standard care group, corresponding to a small amount of deterioration [46]. In this study, an effect size change of 0.3 would be considered a significant finding to stop the study when performing the interim analysis [47]. The reasons for withdrawal from trial by arm will be calculated by the physical therapist.

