## Discussion

This study protocol describes an RCT that is designed to evaluate the efficacy of three-dimensionally integrated exercise on scoliosis measured as Cobb angle, the ATR in degrees, sagittal profile, and quality of life in patients with mild AIS.

In this study, the patients and intervention team are not blinded, because the intervention team needs to carry out the detailed treatment plan with the patients, and the patients in each group know their treatment plan. The assessor, enrollment assistant, and statisticians are blinded with respect to the patients’ treatment allocation. Meanwhile, there are separate rooms for assessment and treatment to avoid having other patients know about the treatment. The control group only needs to perform the assessment at the baseline and after the 6-month intervention, so they will have less time to communicate with the other patients. Once the patient asks to change the treatment plan, they will be eliminated from the study immediately.

Preventing the curve progression is the most important reason for treatment. There is still no intervention to cure AIS [1, 8]. The results of this RCT will provide valuable information for the family, patient, clinicians, and clinical decision makers, as well as to administrative stakeholders, and they may play an important role in providing healthcare services.

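### The statistician is said to be masked, yet handles all data and screens home-exercise compliance, a variable that only experimental patients can have

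*Protocol article*

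**What the plan says.** Masking of the statistician is asserted in four places in the protocol article:

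- Randomization and masking: "The statistician will not be aware of the data coding".
- Data collection, data management, and statistical analysis plan: "All data will be collected, typed, and analyzed by a masked statistician who will not have access to study assignment".
- Interim analysis, which is to be done "by a single statistician who is blinded to allocation and reports the results to the main investigators".
- Discussion: "The assessor, enrollment assistant, and statisticians are blinded with respect to the patients’ treatment allocation".

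The adherence data are described under Compliance supervision: "Compliance will be monitored using a home training diary to record the time and frequency of every-day home training", and "compliance will be calculated as a percentage of the prescribed home exercise dose completed over the course of the 6 months of treatment". Attendance is also expressed as a percentage there. The Assessment section lists exercise compliance among the characteristics to be collected for the experimental group.

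Only one arm is given anything to comply with. Experimental intervention program: "All the patients in the experimental arm will receive treatment of one or two sessions weekly in the hospital", plus a daily session at home. Control group program: "The control group will only attend study assessments and not the therapy sessions".

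Finally, the statistical section names compliance, alongside age, gender, body mass index, Risser sign, time since menarche, apex levels and curve pattern, as a covariable to be screened in univariate models for each outcome. Those reaching p ≤ 0.20 go forward to the multiple models.

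**The concern.** Patients and therapists cannot be blinded in this trial, so its protection against bias rests on the evaluator and the statistician. Coded labels mask an analyst only if nothing else in the dataset shows which code is which. A variable that is defined in one arm and undefined in the other does exactly that.

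Two things are at stake. First, some analytic choices are still open when the data are seen: which covariables to drop for multicollinearity, how to build the weights for missing data, and which sensitivity analyses to run. Made by someone who can see the arms, these choices lose the protection that masking is meant to give. Second, a final report that repeats the protocol's wording would claim a masking that the design did not provide.

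**Working it through.** The plan states no figure on this point, so the check sets its statements side by side.

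**Step 1. In which arm can each field exist?**

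| Field | Experimental (21 planned) | Control (21 planned) |
|---|---|---|
| Home diary | Daily home session prescribed, so a diary is expected | No home programme, so no diary |
| Compliance % | Completed dose ÷ prescribed dose | No prescribed dose, so no denominator |
| Attendance % | Weekly hospital sessions | At most the study assessments |

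Attendance could be stretched to cover control assessment visits. Home-exercise compliance cannot. For a control it must be blank or a constant such as zero, and either value marks the arm.

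**Step 2. Does the statistician hold the field?** There are two separate routes.

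- Data handling: taken at its word, the statistical section passes all data through the statistician.
- Analysis: even if others type the diaries, compliance is a screened covariable for each outcome, so the analyst needs a value for each patient. This route does not depend on how the data-handling sentence is read.

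**Step 3. Do coded labels hide the arm?** Suppose the groups are labelled A and B. Compliance values are filled in under one label and blank or constant under the other. One genuine value under A shows that A is the exercise arm. The field decodes the label.

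**Step 4. How many patients can be identified from the field alone?** Apply the rule that a filled field means experimental and any other means control.

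- All 21 experimental patients have a record: 21 are identified directly and 21 by elimination, so 42 of 42.
- For illustration, assume that the attrition allowed for in the sample size (21 − 19 = 2 per group) leaves two experimental patients with no record at all. Then 19 are identified directly and 42 − 19 = 23 are blank. Of the 23, 21 are controls and 2 are misread. The rule is right for 19 + 21 = 40 of 42, or 95%.

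**Step 5. What does this knowledge reach?**

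- Cobb angle and other assessments: not reached. A separate blinded evaluator does them.
- The p ≤ 0.20 screen: largely mechanical. Knowing the arm does not change a univariate p-value.
- Multicollinearity screening, the weighted estimating equations and the sensitivity analysis: reached, because choices remain open.
- Interim analysis: it concerns Cobb angle only and needs no adherence field. It can stay masked if the field is withheld.

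No section provides for withholding the field, for separate entry, or for release after a lock.

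**The case against.** The strongest reply is that the data-handling sentence is loose and cannot be literal. The evaluator performs the assessments, parents and a therapist verify the diaries, an assistant checks training, and the therapist records adverse events. The protocol does not say who calculates compliance, and a condensed article may leave file structure and release timing to other documents. This stands in part. The absence of a data-flow description is not the point here, and nothing shows that the statistician sees diaries at entry. It does not remove the contradiction, because compliance as a per-patient covariable puts the field in the analyst's hands regardless.

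A reader might also infer more than the documents support:

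- *That every patient's arm is certain at data entry.* Controls are identified by elimination, and an experimental patient without a record could be misread.
- *That an unmasked analyst picks among 2^7 = 128 models, from the seven listed covariables other than compliance.* The count is only an upper bound on subsets. The p ≤ 0.20 rule gives one set for given data, so the number measures no steering.
- *That the interim analysis is unmasked because the same person does it.* The interim section speaks of a single statistician and the Discussion of statisticians in the plural. Neither says that the interim and final analyst are the same person.

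It is also fair to say that analyst masking is a secondary safeguard, and that no effect on the estimate, type I error or power has been shown.

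**Conclusion.** The point holds as an internal contradiction. The protocol claims a masked statistician and also prescribes an analysis that gives that statistician a variable existing in one arm only. From the field alone the arm can be inferred for nearly all of the 42 patients (40 to 42 in the cases worked above), whatever codes are used.

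The consequence is moderate. It concerns the choices left open in the analysis and the accuracy of the reported masking. A reader might go on to conclude that the Cobb results are biased, but the blinded evaluator protects outcome measurement and the documents give no ground for that conclusion.

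The verdict rests on two assumptions: that controls receive no home-exercise prescription, as the intervention and control sections indicate, and that the compliance covariable is analysed per patient, as the covariable screen requires.

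**What to change.** Change the statistical section in two linked ways.

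1. Have the therapist, or the research assistant who already checks daily training and knows the groups, enter diary, attendance and compliance data in a separate file. Withhold that file from the statistician until the primary Cobb analysis has been run and locked under coded labels. The lock should cover the covariable set, the missing-data model and the sensitivity analyses.
2. Remove compliance from the covariable screen for the between-group models. Report it after the lock as a description or an exploratory analysis within the experimental arm. Without this second change the first cannot work, because the plan would still require the field before the lock.

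If the sponsor prefers to keep compliance in the between-group models, the alternative is to delete the claim that the statistician is masked wherever it appears.

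The cost is protocol wording and a second data file, with no extra staff. Adherence results come after the lock, and compliance is no longer a covariable in the between-group models. That second item is a real change to the analysis and should be recorded as one. Little is lost, since the variable has no natural value for controls.

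### The second sample-size justification (21 per group, 95% power for 5 degrees, SD 5) does not follow from its own inputs, derives its SD wrongly and conflicts with the first; no power shortfall is shown

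*Protocol article*

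**What the plan says.** The protocol article justifies its sample size twice.

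**Sample measurement.** This section starts from the group's earlier study, in which "the change of Cobb angle in the experimental group was − 1.55 ± 4.39 degrees" and the control-group change was 2.90 with SD 2.60. With α = 0.05 and β = 0.05 it concludes: "Therefore, we should recruit 19 patients to each group". Ten percent attrition raises this to 21 per group.

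**Data collection, data management, and statistical analysis plan.** This section (the statistical section below) defines the endpoint as a change: "The primary endpoint is the pre- and posttreatment difference in the Cobb angle". It then states that "a sample size of 21 patients per group would be capable of detecting a between-group difference of 5 degrees", with 5% type I error and 95% power, and does not mention attrition. The SD comes from the entry range: "assuming a uniform distribution of Cobb angles in this range (the most unfavorable scenario), an SD of 5 degrees is estimated".

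Neither section says whether the test is one-sided or two-sided.

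**The concern.** A difference of 5 with an SD of 5 is a standardised difference of 1.0. For 95% power that needs more than 21 per group, so the stated power looks too high for its inputs. The route to the SD looks wrong in two ways: a uniform distribution over 10 degrees does not have an SD of 5, and the spread of angles at entry says nothing direct about the spread of changes over six months. The two sections also give different grounds for the same number of patients.

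At stake is whether the protocol's power statement can be relied on and reported. A reader who wants to know what the trial was designed to detect finds two incompatible answers, and the arithmetic of one does not hold.

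**Working it through.** **Method.** Two independent means, 1:1 allocation, α = 0.05, noncentral t with 2n − 2 degrees of freedom and noncentrality d√(n/2). Normal-approximation results are given where they differ.

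**1. The first calculation (Sample measurement) reproduces, but only two-sided.**
- Difference: 2.90 − (−1.55) = 4.45.
- Pooled change SD: √[(4.39² + 2.60²)/2] = 3.61.
- d = 4.45/3.61 = 1.233.
- Required n for 95% power: two-sided 18.1, so 19 per group; one-sided 15.
- The stated 19 is therefore a two-sided result, with power 95.9%.
- Attrition: 19 × 1.1 = 20.9, so 21. Conversely 21 × 0.9 = 18.9, so about 19 completers are expected.

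**2. The second calculation (statistical section).** d = 5/5 = 1.0. The noncentrality is √(21/2) = 3.24 with 21 per group and √(19/2) = 3.08 with 19.

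| Analysed per group | Two-sided power | One-sided power |
|---|---|---|
| 21 | 88.5% (normal 90.0%) | 93.8% (normal 94.5%) |
| 19 | 85.1% (normal 86.9%) | 91.6% (normal 92.5%) |

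For 95% power at d = 1.0, 27 evaluable per group are needed two-sided and 23 one-sided (normal: 26 and 22).

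**3. The SD of 5.**
- A uniform distribution on 10 to 20 has SD (20 − 10)/√12 = 2.89.
- On that range 5 is the half-width and the largest possible SD. It is reached only if half the patients enter at 10 and half at 20, so uniform is not the least favourable case.
- If 2.89 were used instead, 10 per group would give 95% power two-sided, so that does not lead to 21 either.
- The endpoint is change. If the SD were 5 at each visit and the pre-post correlation were ρ, the change SD would be 5√[2(1 − ρ)], which equals 5 only at ρ = 0.5. The document gives no ρ. For assumed values of 0.3 to 0.7 the change SD runs from 5.9 to 3.9, and two-sided power for 5 degrees with 21 per group from 76% to 98%.

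**4. The two sections side by side.**

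| | Sample measurement | Statistical section |
|---|---|---|
| Difference | 4.45 | 5 |
| SD | 3.61 (pooled, of change) | 5 (from entry range) |
| Number giving 95% power | 19 | 21 |
| Role of 21 | includes 10% attrition | gives the power itself |

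**5. Power for 5 degrees with the change SDs that the document supplies.** d = 5/3.61 = 1.386. Two-sided power is 99.2% with 21 per group and 98.6% with 19. Two-sided power for 5 degrees stays at 95% or more for a change SD up to about 4.38 with 21 per group, or 4.16 with 19.

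**The case against.** **The one-sided reading.** The statistical section does not state sidedness. One-sided, with all 21 analysed, power is 93.8% to 94.5%, close to the stated 95%, so it is too blunt to call the figure false without conditions. What stands is that the shortfall on that reading is about one percentage point. But it requires no attrition, although the 21 in Sample measurement already allows for 10%; with 19 analysed, power is about 92%. It would also make the two sections use different tests, because the 19 reproduces only two-sided.

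**The trial has enough power anyway.** This is the stronger objection, and it stands. A reader might infer from the 88% and 85% that the trial is underpowered, or that its type II error is really 11% to 15%. The document does not support that. Those figures depend on a change SD of 5, the very value shown above to have no valid derivation. On the only change SDs in the document, power for 5 degrees exceeds 98%.

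**The 5 degrees as a clinical threshold.** A reader might also say that the trial misstates its power for its own clinically significant effect. The Suspension criteria section applies 5 degrees to an individual patient's change and ties it to radiographic reliability. It does not set it as a difference between group means.

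**SD 5 as a cautious choice.** Five is an upper bound for the spread of entry angles on the 10 to 20 range. It is not an upper bound for the SD of change, which exceeds 5 if the correlation is below 0.5 in the calculation above.

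**Conclusion.** The point holds as an error in a stated power and in its derivation. From its own inputs, the second justification gives about 88% two-sided or 94% one-sided with 21 analysed, and 85% or 92% with 19. It does not give 95%. The SD of 5 does not follow from a uniform distribution and describes the wrong variable. The two sections disagree on the difference, the SD and the meaning of 21.

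It does not hold as evidence that the trial is too small. The calculation in Sample measurement is sound on its inputs: 19 completers per group give about 96% two-sided power for 4.45 degrees and 98.6% for 5 degrees.

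The conclusion rests on three assumptions. The figures are for a two-sample t test on change, a simplification of the planned mixed models. Two-sided is inferred from the reproduced 19 and is not stated. The 3.61 comes from the earlier study, which the Background cites among 3-month studies, so the SD of a 6-month change could differ. That is a reason to show one sensitivity figure.

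**What to change.** - Delete the power sentence and the uniform-distribution sentence from the statistical section, and refer there to Sample measurement as the only basis.
- State in Sample measurement that the test is two-sided at 5%, and that 19 is the evaluable number and 21 the recruited number.
- Restate power for 19 completers per group at a pooled change SD of 3.61: about 96% for 4.45 degrees and 98.6% for 5 degrees.
- Add, labelled as a sensitivity figure only, that if the change SD were 5, two-sided power for 5 degrees would be about 85% with 19 and 88% with 21 per group.

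This is a text correction. Enrolment, design and analysis do not change.

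### Adjustment covariables, including post-randomisation compliance, are chosen by a univariate p ≤ 0.20 screen on the trial's own outcomes, which harms the between-group estimate if change is modelled

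*Protocol article*

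**What the plan says.** The section on data collection, data management and statistical analysis sets a two-step rule. Step one: "To screen for variables associated with each of the outcome variables, univariate linear mixed models for each relevant covariable". The candidates are listed: "age, gender, body mass index, Risser sign, time since menarche, apex levels, curve pattern, and compliance may have associations with risk of progression". Step two fits multiple linear mixed models for each time point, "including covariables found significant at *p* ≤ 0.20 in the univariate analysis, and after screening for multicollinearity". The same section later says that group changes from baseline to 6 months are assessed with adjustment for covariables.

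No covariable is fixed in advance, and no cut-off is given for the multicollinearity step. The text does not say whether treatment is in the univariate models, or whether selected covariables enter as main effects or by time.

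Compliance is defined under Compliance supervision: "compliance will be calculated as a percentage of the prescribed home exercise dose completed over the course of the 6 months of treatment". Under Control group program, controls attend assessments only.

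The sample size comes from an unadjusted two-group comparison of change: "Therefore, we should recruit 19 patients to each group".

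**The concern.** The outcome that is to be compared between arms also decides what the comparison is adjusted for, in about 38 to 42 patients and afresh for each outcome.

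The direction of the harm follows from the algebra. Write the change as y = τ·g + e, with g the arm and z a baseline covariable unrelated to e.

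- With treatment left out, the screen looks at the covariance of z with y. This is τ × cov(z, g) + cov(z, e).
- It is largest when the chance imbalance (through τ) and the chance noise point the same way, so z is picked more often in those trials.
- The adjusted effect is the raw difference minus b × (imbalance in z), where b reflects cov(z, e). In the trials where z is picked, the subtracted term tends to have the sign of τ, so the estimate moves toward zero.

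The assumed effect is large (about 1.23 SD), so the first term matters. At stake are some dilution of the primary estimate, some power, and intervals that cover a little less than stated.

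Compliance is a separate and potentially larger problem. Only the exercise arm has a prescribed dose, so the variable is close to a second copy of the arm indicator.

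**Working it through.** **Inputs.** From Sample measurement: "the change of Cobb angle in the experimental group was" −1.55 ± 4.39 degrees, and "in the control group, it was 2.90 ± 2.60 degrees"; α 0.05, β 0.05; 19 per arm, 21 after attrition. From the statistical section: a second power statement with 5 degrees, SD 5 and 21 per arm. The documents give no covariable-outcome correlation, so prognostic strength (R²) is assumed over 0 to 0.4.

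**Step 1: the plan's own figure.** Difference = 2.90 − (−1.55) = 4.45. Pooled SD = √[(4.39² + 2.60²)/2] = √13.016 = 3.61. d = 4.45/3.61 = 1.23. A two-sided t test has 94.9% power at 18 per arm and 95.9% at 19, so 19 reproduces. At 21 per arm it has 97.4%.

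**Step 2: how often the screen picks noise.** With six independent, non-prognostic candidates, P(at least one p ≤ 0.20) = 1 − 0.8⁶ = 0.74. Simulation gives 72 to 73%.

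**Step 3: treatment outside the screen, change modelled.** Seven independent single-parameter baseline covariables, 12,000 trials per row. The fixed short set holds only the truly prognostic covariables (none when R² = 0).

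| Design | R² | Power, screened | Power, fixed short set | Power, all 7 fixed | Shrinkage |
|---|---|---|---|---|---|
| 19/arm, 4.45 | 0 | 92.9 | 95.9 | 90.4 | 5.9% |
| | 0.1 | 94.5 | 96.5 | 93.4 | 6.3% |
| | 0.2 | 95.3 | 97.3 | 95.2 | 7.1% |
| | 0.4 | 98.2 | 99.4 | 98.4 | 6.4% |
| 21/arm, 4.45 | 0 | 95.4 | 97.2 | 94.0 | 5.3% |
| | 0.1 | 96.6 | 97.9 | 95.8 | 5.8% |
| | 0.2 | 96.9 | 98.6 | 96.8 | 6.3% |
| | 0.4 | 99.2 | 99.8 | 99.3 | 5.7% |
| 21/arm, 5 with SD 5 | 0 | 85.4 | 88.7 | 82.0 | 5.6% |
| | 0.1 | 86.4 | 89.7 | 84.8 | 6.3% |
| | 0.2 | 88.7 | 92.2 | 88.7 | 6.4% |
| | 0.4 | 95.1 | 97.3 | 95.4 | 5.3% |

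The loss against the short set is 0.6 to 3.5 points. Against fixing all seven, screening ranges from 3.4 points better to 0.3 worse. Type I error is 4.7%.

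**Step 4: covariable coding.** Curve pattern has four classes and apex level is naturally categorical. Six baseline candidates (age, sex, body mass index, Risser sign, curve pattern, apex level), 4,000 trials per setting, compared with age fixed in advance:

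- 19/arm, none prognostic, Risser and apex linear: estimate 4.21 against 4.47 (5.8% less); power 93.4 against 96.0; coverage 94.1%.
- Same, Risser and apex as factors: 4.09 against 4.43 (7.7% less); power 90.7 against 95.3; coverage 93.7%.
- Age correlated 0.4 with outcome, factors: 4.12 against 4.41 (6.6% less); power 93.7 against 97.7.
- 21/arm, 5 degrees, SD 5, factors, none prognostic: 4.66 against 5.02 (7.2% less); power 82.6 against 88.1.

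**Step 5: treatment inside the screen.** Shrinkage is about 0%. Type I error is 6.4% with seven single-parameter covariables and 7.3% with factors.

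**Step 6: mixed model on two rows per patient.** In one simulated complete data set the group-by-time estimate was −3.188 without the covariable, −3.188 with its main effect, and −4.623 with a covariable-by-time term. A main effect alone therefore leaves the estimate unchanged. Steps 3 to 5 apply to a model of the change, or to one with covariable-by-time terms.

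**Step 7: compliance.** Assume 0 in controls, and mean 0.8 with SD 0.1 to 0.2 in the exercise arm. Variance between arms = 0.25 × 0.8² = 0.16. Average variance within arms = 0.5 × SD² = 0.005 to 0.02. VIF = 1 + 0.16/0.02 = 9 to 1 + 0.16/0.005 = 33. Simulated trials gave about 12 to 37, with values capped at 100%. Compliance passed p ≤ 0.20 in 96 to 99% of trials. If it is kept with arm in the model, power falls to about 8 to 25%.

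**The case against.** The strongest reply is that the figures are not fixed by the text, and much of this stands.

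- Whether treatment is in the screen is not stated. If it is, the shrinkage goes. That does not rescue the rule, because type I error then rises.
- The plan speaks of mixed models and of weighted estimating equations. With complete data and covariable main effects only, the treatment estimate does not move. This is a real limit. However, the same section defines the primary endpoint as the pre-to-post difference and fits models for each time point, so a model of the change is a natural reading.
- The power loss depends on the comparator. Nobody knows the truly prognostic set in advance, and against fixing the whole list there is no clear loss. At 21 per arm and 4.45 degrees, with single-parameter covariables, every loss is below 2 points.
- The candidate list and threshold are stated beforehand and the statistician is masked, so this is a fixed algorithm rather than free choice. The bias is conservative and amounts to a few tenths of a degree, against the 5 degrees the protocol treats as the smallest meaningful change.

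A reader might infer that the planned 95% power is mostly lost. The runs do not support that: at 4.45 degrees, screened power in the Step 3 table still reaches 95% in six of eight settings. Nor is it a defect in itself that outcomes may end up with different covariables, since prognostic factors can differ by outcome.

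On compliance, the coding in controls is not stated, and the multicollinearity step ("in the univariate analysis, and after screening for multicollinearity") might remove it. But with no cut-off given, nothing in the text ensures that compliance rather than another term is dropped.

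**Conclusion.** The rule is stated in the protocol and should be changed. It is not a detail left to a later analysis plan.

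If treatment is outside the screen and change is modelled (or covariables enter by time), the estimated effect shrinks by about 4 to 8%. Roughly 1 to 5 points of power are lost against a short fixed baseline set at 4.45 degrees and 19 to 21 per arm, with coverage of about 94% and type I error of about 5%. The range reflects assumed covariable coding and prognostic strength. If treatment is inside the screen, there is no shrinkage but type I error is about 6.4 to 7.3%. So under a model of the change, the rule worsens inference on either reading.

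It would go too far to say that the primary estimate is biased toward no effect without qualification: a complete-data two-row mixed model with main effects only is untouched.

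Listing compliance as a candidate is wrong on any of these readings, because it arises after randomisation and is defined for one arm only. The size of that harm rests on the assumed coding of 0 in controls and on compliance surviving the collinearity step.

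**What to change.** Delete the p ≤ 0.20 screen for the between-group comparison. Name in advance two or three baseline covariables that stay in the model whatever their p-value, for example the baseline value of the outcome and either age or Risser sign (these two overlap, so one is enough). Remove compliance from the treatment-effect model. Keep the wider list, if wanted, as a risk-factor analysis labelled exploratory, with arm in the model.

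The cost is a sentence or two in the analysis section, and about 0.5 point of power for each fixed covariable that proves non-prognostic. No change to sample size or data collection is needed.
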